## Follow-up clinic visits (non study drug administration visits)

Parents will be asked to bring enrolled infants back to the clinic for follow up visits at 18 weeks, and at 12, 18, and 24 months. A compliance monitor will visit the houses of families who fail to appear within 2 weeks of a follow-up visit. To facilitate the work of compliance monitors, a photograph of each mother and child will be made at enrolment, and that photograph kept with a map locating the place of residence. These documents will be returned to the mother at the conclusion of the study or destroyed.

At the 18-week visit, blood (from the same finger prick) will be obtained and frozen at –70C for later determination of post-vaccination serologic testing for antibodies to polio, diphtheria, tetanus, hepatitis B, and Hib. At the 12-month visit, blood will be obtained for determination of sickle cell trait and frozen for later determination of measles antibody titer. Blood will also be collected on filter paper for later testing of genetic markers for drug resistance.

A questionnaire (identical to that administered during the intervention visits) soliciting information about overall health of the baby, febrile episodes, other intercurrent illnesses, use of other medications, ITN usage, and compliance with iron will be administered.

The algorithm for antimalarial treatment of children who are febrile at the 18 week, and at 12, 18, and 24 month visits will be the same as for the intervention visits, with the exception that all infants who need treatment will be provided quinine (18-week visit) or Coartem (12, 18, and 24-month visit if the child weighs at least 5 kg), as no children will be receiving study drugs at these visits. Children weighing less than 5 kg requiring antimalarial treatment will receive quinine. Children with severe malaria will treated with quinine, regardless of age. Infants with Hb<8 g/dl at the 12, 18, or 24-month visits will be treated with iron per the national policy.

#### Note: Coartem (Artemether-Lumefantrine [AL])

Coartem is being provided as a treatment for clinical malaria in children who have made their 12 month visit. It is not an experimental drug, and is not being evaluated in this study. It does not constitute part of the experimental procedures of the study.

Coartem is a highly efficacious antimalarial drug, and is a combination of Lumefantrine, is a novel aryl amino alcohol antimalarial and artemether, one of the artemesinin drugs (that includes artesunate). Coartem is more costly than SP - a subsidized adult course costs approximately 200 KSh, or $2.40, while an unsubsidized adult course of Coartem cost 400 Ksh, or 5 USD. Coartem is a registered product in Kenya. Coartem is a first-line drug for the treatment of malaria in Kenya. Coartem is the primary antimalarial recommended by the World Health Organization for treatment of uncomplicated malaria in countries with antimalarial drug resistance.

Existing data suggest that this ACT is safe and that the efficacy of Coartem is high (Hassan Alin, Bjorkman et al. 1999; van Vugt, Ezzet et al. 1999; Ezzet, van Vugt et al. 2000). There have been no significant side effects reported from the use of artemether in humans. Most studies report adverse events as mild or moderate in severity (including dizziness, headache, anorexia, nausea and abdominal pain), noting that these events may also be attributable to malaria (Hatz, Abdulla et al. 1998; van Vugt, Ezzet et al. 1999; van Vugt, Looareesuwan et al. 2000)

Home visit

At 6 months of age, a home visit will be made to check on compliance with iron administration. At this visit, the compliance monitor will ask questions about iron administration, and will measure the amount of iron remaining in the bottles.

## Unscheduled visits

Parents of enrolled infants will be instructed to take them to one of the study health facilities for evaluation and treatment of all illnesses. Study infants who make such unscheduled visits for febrile illness during the study period will have a malaria RDT performed. Those with a positive RDT will be treated with a treatment course of quinine if they present before their 12-month visit. Treatment with quinine (instead of SP or Coartem) will avoid the possibility of giving doses of SP or artemisinin that are too closely spaced in time while the child is receiving study drugs. Those with a positive RDT at or after their 12-month visit will receive Coartem, unless they weigh less than 5 kg, in which case, they will receive quinine. All children who are febrile will also have a malaria blood film performed at the same time. All children who have a blood sample taken for malaria diagnosis or have signs or anemia will also have a hemoglobin measurement performed. If any infant who had documented fever but was negative for malaria by RDT is later found to have malaria by microscopy, the results and a treatment course of quinine (or Coartem) will be delivered to the infant's home. Blood from the same finger-stick blood sample will be dried on to filter paper for analysis on molecular markers of antimalarial drug resistance.

During weekends and evenings, a nurse will be available to assist IPTi participants who are severely ill. The nurse will be stationed at Lwak hospital, our most central study clinic. In cases where the infant must be hospitalized, the nurse will provide stabilizing treatment and the IPTi Field Supervisor, Coordinator, or designee will arrange transport to Bondo or Provincial hospital.

Any child that has an allergic reaction (severe cutaneous reaction, anaphylaxis, or other severe reaction) associated with any study drug will be withdrawn from receiving further study drug. The study code will be broken for that child, so that a determination of possible drug allergy can be determined. Parents will be informed about the possible allergy, and that information will be recorded on the child health card. If future treatment for malaria is needed, parents will be informed that it should be carried out with a drug other than one in the class to which the child had a reaction. The child will continue to be followed as per protocol with the exception that the child will not receive any additional doses of study medication. The parent or guardian maintains the right to completely withdraw the child from the trial at any time (meaning that no further follow-up would occur).

# Laboratory procedures

Thick blood smears made from capillary blood will be stained with 2-3% Giemsa stain (pH 7.2) for 45 minutes and examined for parasites. Parasites and leukocytes will be counted in the same fields until 500 leukocytes are counted. Parasite densities will be estimated using an assumed leukocyte count of 8,000 leukocytes per l of blood. The limits of detection are estimated at <10 parasites/l of blood.

Dried filter papers will be sent to the London School of Tropical Medicine and Hygiene for analysis of molecular markers of resistance. Although capacity exists in Kenya to conduct this analysis, this central reference lab will be used by all study sites for this analysis, to ensure quality assurance and comparability of results across IPTi sites. To further develop molecular analysis capacity at KEMRI/CDC, one laboratory technician from KEMRI/CDC will travel to London to analyze the samples in the central laboratory.

Capillary blood will be collected in a microcuvette and examined in a Hemocue machine to determine the Hb level. Capillary blood will also be collected into a Microtainer tube for sickle cell testing, and EPI vaccine antibody testing. Analysis of serologic response to EPI vaccines will be performed by the Pasteur Institute in France or another comparable laboratory selected by WHO.

Sickle cell testing will be done in Kenya using a standard Hb electrophoresis technique. Testing for glucose-6-phosphate dehydrogenase genotype will be performed by polymerase chain reaction (PCR). For the primary analysis of the immune response to Hib vaccine, concentrations of anti-PRP antibody will be compared in the SP and placebo groups at 18 weeks. As part of the secondary analysis, the immune response to vaccine among children in the placebo group who have symptomatic malaria, asymptomatic malaria, and no malaria will be evaluated.

Immediately after nasopharyngeal swabs are obtained they will be placed in a culture media, consisting of skim milk, glycerol and glucose (STGG). The swab tip will be cut off into the STGG media and the media will be refrigerated until ready for transport. Cryotubes with the swabs in the STGG media will be frozen at -70oC at the laboratory in Kisian. When ready for processing, 100 l of the STGG-bacteria mix will be thawed and spread on a Hib halo plate, allowing the fluid to be absorbed before inverting the plate. The Hib halo agar is made as a chocolate agar medium with the addition of bacitracin and 1 ml of anti-Hib serum. In order to transfer technology and build KEMRI/CDC laboratory capacity, we propose to sponsor one or two KEMRI/CDC laboratory staff to come Atlanta to acquire the technical skills to conduct this testing. This training will then be followed up by visits to the KEMRI/CDC laboratory from senior CDC/Atlanta staff for quality assurance.

#

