## Impact of routine antimalarial usage on response routine vaccinations

In order for this intervention to have a programmatic future, it must be convincingly demonstrated that IPTi does not have a negative effect on the development of antibodies to routinely administered vaccinations. This will be achieved by comparing the proportion of infants in the intervention (IPTi) and placebo groups that attain post-vaccination geometric mean antibody titers (GMTs) above a pre-defined protective level for each EPI vaccine.

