## Secondary objectives

1. Compare the efficacy of iron supplementation plus IPTi with one of 3 antimalarial regimens (SP/AS3, Lapdap [chlorproguanil-dapsone], or AQ/AS3) given at routine EPI visits with iron supplementation alone (+ placebo) on the prevention of moderate and severe anemia in the first year of life.
2. Assess the impact of IPTi with the aforementioned regimens on serologic responses to EPI vaccines (Polio, Diphtheria, Tetanus, Pertussus, Hepatitis B, *Hemophilus Influenzae* type B, and Measles).
3. Assess the impact of IPTi with the aforementioned regimens (particularly SP/AS3) on the nasal carriage rates of *Haemophilus influenza* type b.
4. Compare the efficacy of iron supplementation and IPTi with one of 3 antimalarial regimens (SP/AS3, Lapdap [chlorproguanil-dapsone], or AQ/AS3) given at routine EPI visits with iron supplementation alone (+ placebo) on the prevention of all-cause hospitalization in the first year of life.

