## Sample Size

This study primarily aims to determine if routine intermittent treatment with antimalarials results in a reduction in childhood clinical malaria, by assessing time to first episode of clinical malaria.

We estimate that the median time to first episode of clinical malaria in the placebo group receiving iron is 18 months (68 weeks after the first intervention visit). The sample size required for 90% power to detect a protective efficacy of 40%, assuming =0.017, is 250 per arm. Alpha has been adjusted to 0.017 in order to account for multiple comparisons (3 arms each compared to the placebo group, Bonferroni adjustment 0.05/3 tests=0.017). Therefore, the study would require a total sample of 1000 infants (250 in each of 4 groups). We expect that 11% of infants will have the outcome measure at baseline and thus will be excluded from the primary analysis. Including this decrease and adjusting for a 10% loss to follow up and 13% mortality, the study will require 1516 infants (379 in each arm).

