**Data Management**

Data cleaning and storage:

Quantitative data will be entered using scan-ready forms and an optical scanner. Data will be entered and edited in Kenya. Images of scan forms will be kept on a secure server with access limited to study personnel. Data analysis will be undertaken collaboratively in Kenya and at CDC in Atlanta. Access to study computers will be restricted to study personnel, and paper records will be secured in locked cabinets in Kenya. Paper records will not be transported to Atlanta. Electronic files will be transferred to Atlanta either as password-protected e-mail attachments or as password protected files on zip disks or CDs.

Sample storage

Specimens will be stored in locked freezers or cabinets with identifiers at KEMRI and at CDC, to which only study personnel will have access.

In accordance with WHO advice, testing for serological responses to EPI antigens will be performed at a single commercial reference laboratory. The commercial laboratory will only have coded specimens, and will not be engaged in the research. Any remaining sera will be shipped back to Kenya.

Statistical analysis:

SAS software (SAS Institute, Cary, NC), and STATA software (STATA corporation, College Station, TX) will be used for quantitative data analysis. The primary analysis will be based on intention to treat. The analysis will be time to first clinical malaria comparing each of the study drug arms to the placebo arm. Mild, moderate, and severe anemia will also be compared between each study drug arm and the placebo arm.

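### The primary Hib vaccine-response analysis compares SP with placebo only, although the objective covers all three regimens, and its outcome scale differs from the one set elsewhere for every vaccine

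*Protocol*

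**What the plan says.** Four places in the protocol bear on vaccine response.

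- **Secondary objectives, item 2:** "Assess the impact of IPTi with the aforementioned regimens on serologic responses to EPI vaccines". The regimens are SP/AS3, Lapdap and AQ/AS3, and Hib is among the vaccines listed.
- **Impact of routine antimalarial usage on response routine vaccinations:** this section makes programme use depend on one condition, namely that "it must be convincingly demonstrated that IPTi does not have a negative effect on the development of antibodies to routinely administered vaccinations". The stated means is "comparing the proportion of infants in the intervention (IPTi) and placebo groups that attain post-vaccination geometric mean antibody titers". The cut-off is a protective threshold set in advance, and all the EPI vaccines are covered.
- **Laboratory procedures:** the primary analysis for Hib is that "concentrations of anti-PRP antibody will be compared in the SP and placebo groups at 18 weeks". The secondary analysis mentioned there stays within one arm: "the immune response to vaccine among children in the placebo group who have symptomatic malaria, asymptomatic malaria, and no malaria will be evaluated".
- **Data Management, Statistical analysis:** clinical malaria is compared between each drug arm and placebo, and "Mild, moderate, and severe anemia will also be compared between each study drug arm and the placebo arm". Serology is not mentioned.

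**The concern.** The protocol makes absence of vaccine interference a condition for using IPTi in programmes, and its Justification values alternatives to SP as resistance rises. Lapdap and the amodiaquine combination are those alternatives. The one comparison that the protocol calls primary for Hib leaves both out. If either drug blunted the anti-PRP response, that analysis could report no difference between its two groups and be entirely correct about them, while the answer that policymakers need for the other two regimens came from no designated analysis.

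The scale is unsettled as well. For the same antigen, one section compares concentrations and another compares proportions above a threshold. The background text on Hib carriage gives two thresholds, 1 for protection against invasive disease and 5 for protection against carriage, in the same concentration unit. A protective level for Hib is therefore not a single number until one is named.

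**Working it through.** **Side by side, for Hib**

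| Place | Arms | Outcome | Status |
|---|---|---|---|
| Secondary objective 2 | All three regimens | Serologic response | Objective, no test fixed |
| Background, vaccine response | IPTi and placebo, regimens not listed | Proportion above a protective level | Stated method for each EPI vaccine |
| Laboratory procedures | SP and placebo | Anti-PRP concentration at 18 weeks | Named primary analysis |
| Statistical analysis | Each drug arm vs placebo | Malaria and anemia only | Silent on serology |

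The second and third rows both fix a method for Hib, on different scales, and the third is narrower in arms than the objective. No sentence ranks them.

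**How much the primary Hib contrast omits**

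Sample Size gives 250 evaluable and 379 enrolled per arm. The inflation reproduces: 250 / (1 − 0.11 − 0.10 − 0.13) = 250 / 0.66 = 378.8, so 379, and 4 × 379 = 1516. Two omitted arms are 2 × 379 = 758 infants, half of the enrolment. Since neither arm enters the comparison, an effect of either drug cannot change its result.

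**Conditional check: dilution if the background sentence means all IPTi arms combined**

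The protocol states no power, alpha, margin or response rate for serology, so these inputs are assumptions:
- 250 infants per arm, borrowed from the malaria sample size;
- 90% above the threshold on placebo;
- one regimen at 80%, the other two at 90%;
- two-sided tests.

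The pooled IPTi rate is (0.90 + 0.90 + 0.80) / 3 = 0.867. The 10-point drop shows as 10 / 3 = 3.3 points.

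Power = Φ[(d − z·SE0) / SE1], where SE0 uses the common proportion and SE1 the separate ones.

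- Affected arm vs placebo (250 vs 250): SE0 = √(0.85 × 0.15 × 2/250) = 0.0319; SE1 = √(0.09/250 + 0.16/250) = 0.0316.
  - Alpha 0.05: (0.100 − 1.960 × 0.0319) / 0.0316 = 1.18, power 88%.
  - Alpha 0.017, the level used for the efficacy endpoint ("Bonferroni adjustment 0.05/3 tests=0.017"): (0.100 − 2.387 × 0.0319) / 0.0316 = 0.75, power 77%.
- Pooled IPTi vs placebo (750 vs 250), alpha 0.05: SE0 = √(0.875 × 0.125 × (1/250 + 1/750)) = 0.0242; SE1 = √(0.09/250 + 0.1156/750) = 0.0227; (0.0333 − 1.960 × 0.0242) / 0.0227 = −0.62, power 27%.

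Range for a 10-point drop in one arm, 250 per arm:

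| Assumed placebo rate | Arm-wise, alpha 0.017 | Arm-wise, alpha 0.05 | Pooled, alpha 0.05 |
|---|---|---|---|
| 95% | 91% | 96% | 40% |
| 90% | 77% | 88% | 27% |
| 80% | 58% | 73% | 19% |

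With 200 to 300 per arm and rates of 90% and 80%, arm-wise power at 0.05 is 80% to 93%, and pooled power is 22% to 32%.

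**The case against.** The SP comparison may be a deliberate priority for Hib. The background argues that malaria itself may depress the response to the conjugate vaccine, and the analysis of placebo infants by malaria status follows from that. Naming one primary comparison does not cancel objective 2 for the other arms, and the secondary item is introduced as part of a larger set. This explains why SP may have been singled out, but it does not reconcile the text. The special emphasis on SP/AS3 is attached to the carriage objective (item 3), not to the serology objective (item 2), and no sentence gives Lapdap or AQ/AS3 a Hib analysis.

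Three stronger readings are tempting, and the protocol does not support them.

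- **That three incompatible tests are fixed.** Objective 2 is an objective and conflicts with neither method. The conflict lies between two sections.
- **That the plan pools the arms.** "comparing the proportion of infants in the intervention (IPTi) and placebo groups" never says so. An arm-by-arm reading fits the four-arm design, the three-way alpha split and the statistical analysis section. The dilution figures depend on the other reading.
- **That the contrast can be picked after the data are seen.** A statistical analysis plan may exist and is not at hand, and it may settle the order of secondary serology contrasts.

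The illustration has further limits. Every response rate in it is assumed. The 250 per arm follows an exclusion for malaria at baseline that would not apply to an antibody sample. And demonstrating absence of harm is a matter of confidence limits against a margin, for which power to detect a difference is only an indirect guide.

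**Conclusion.** The point holds, in a narrow form. The protocol's primary Hib analysis is restricted to SP and placebo, against an objective that covers three regimens and names Hib. Its scale differs from the one set for every EPI vaccine. That much follows from the text without any assumption: two of the three drug arms contribute nothing to the primary Hib analysis, so it cannot detect interference by Lapdap or AQ/AS3.

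Outright omission concerns Hib alone; for the other vaccines no sentence limits the comparison to SP. Loss of power through pooling is a possible consequence of an ambiguous sentence. If the arms were combined, a one-drug effect would shrink to one third. The figures of 77% or 88% against 27% rest on that reading and on assumed rates. Neither outcome scale is wrong in itself; the defect is that Hib has two and neither is ranked. An analysis plan that follows the laboratory section inherits the gap, and one that departs from it contradicts the protocol.

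**What to change.** - **Laboratory procedures:** extend the primary Hib comparison to each drug group (SP/AS3, Lapdap, AQ/AS3) against placebo at 18 weeks.
- **Background section on vaccine response:** say each IPTi regimen and placebo, which matches the contrast already used for malaria and anemia. If a combined IPTi comparison is wanted, label it supportive.
- **Hib scale:** state whether concentration or the proportion above a threshold is primary, make the other supportive, and name the threshold, since the background gives two. Which scale leads is the sponsor's choice.
- **Secondary objective 2** needs no change.

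No new procedure is required. Blood for EPI antibodies is scheduled for infants without restriction by arm (Enrollment, Follow-up clinic visits, Study Schedule). Any assays on the two added arms that are not already planned would be an extra cost. The statistical cost is three contrasts per antigen in place of one, with wider intervals than a combined comparison. There is a multiplicity cost if alpha is split: in the illustration, arm-wise power falls from 88% to 77%.

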## Quality control

A randomly selected 10% sample of malaria blood films will be re-read by an independent microscopist for quality control purposes.

The Hemocue machine will be compared against a known standard after every 20 samples. The Hemocue machine will be calibrated weekly or whenever it reads a difference of +/0.3 g/dl from the known standard.

# Definitions

# A clinical malaria episode in an infant will be defined as an axillary temperature of at least 37.5C in combination with asexual *P. falciparum* parasitemia of any density . Mild-to-moderate anemia will be defined as Hb <11.0 and 8. Severe anemia will be defined as Hb <8 and 5. Critical anemia will be defined as Hb <5.

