# Iron deficiency and malaria as risk factors for anemia

Iron deficiency and malaria have been regarded as the predominant causes of anemia among African children. Their relative contribution depends on age, season and geographical area, reflecting local and time-dependent patterns in the availability of iron-containing foods and malaria transmission. Children are at highest risk for either iron deficiency anemia or malarial anemia between 6 and 36 months of age.

In preschool children, iron deficiency predominantly results from a poor dietary intake of iron coupled with rapid body growth. Although hookworm and schistosomiasis may be contributory factors in children in this age range, during infancy the prevalence and intensity of these infections is low in western Kenya: 4.0% for hookworm, and 0% for *Schistosoma mansoni* in children aged <12 months ([name], CDC/KEMRI, personal communication).

For children < 5 years of age, the overall incidence of severe malarial anemia (Hb < 5 g/dl) is estimated at 15-60 cases per 1,000 children per year [2]. In addition, malaria-associated severe anemia is an important cause of hospital admissions in malaria-endemic areas. In one hospital in Malawi, nearly 10% of admissions were for malaria-related severe anemia; the peak prevalence occurred among infants aged 6-11 months (15%) [7]. These rates were lower in children admitted to a hospital in an area not holoendemic for malaria [7]. Other studies have confirmed that the burden of malaria-related anemia falls primarily on infants and young children [3, 4]. Infants enrolled in a cohort study in a holendemic area in western Kenya had a hemoglobin nadir at 9-12 months of age which was 3.0 g/dL below the mean hemoglobin for age among children in non malarious areas [4]. In that same study, nearly one-third of infants 7-12 months of age had moderate or severe anemia (hemoglobin <8 g/dL), and more than three- quarters had some degree of anemia (hemoglobin < 11 g/dL) [4]. Further evidence from this same cohort suggests that infants and young children have a significant risk of anemia even with low density parasitemia, which may not be associated with fever or clinical illness [15]. It is increasingly recognized that in areas with intense malaria transmission the slow insidious process of repeated, often ‘asymptomatic’ (not associated with fever) malaria infections, leads to chronic anemia and is a major cause of severe anemia and malaria-associated death [16].

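### Anemia is defined in exclusive bands that do not match the categories in secondary objective 1 and the analysis: moderate has no cut-off, an Hb below 5 is in no stated efficacy comparison, and the 8 to <11 band does not track benefit.

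*Protocol*

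**What the plan says.** The protocol's Definitions section gives three categories: "Mild-to-moderate anemia will be defined as Hb <11.0 and 8"; "Severe anemia will be defined as Hb <8 and 5"; and "Critical anemia will be defined as Hb <5". The comparison signs before 8 and 5 are missing from the text at hand and are read here as at or above. Their absence is not treated as an error in the plan. Two bounds per category, with a separate category underneath, make these exclusive bands.

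Secondary objective 1, repeated in the Executive Summary, compares each regimen with placebo "on the prevention of moderate and severe anemia in the first year of life". The statistical analysis paragraph under Data Management says: "Mild, moderate, and severe anemia will also be compared between each study drug arm and the placebo arm".

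The background section on iron deficiency and malaria reports that "nearly one-third of infants 7-12 months of age had moderate or severe anemia (hemoglobin <8 g/dL", so there moderate or severe means everything below 8. It also reports that more than three-quarters of these infants had Hb <11. The Executive Summary and the background on prevention cite the Tanzanian trial's severe anemia result as Hb <8, with no lower bound given.

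**The concern.** The objective, the definitions and the analysis use three different sets of categories. This has three consequences.

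1. **Moderate is undefined.** It is named in the objective and in the analysis, but the Definitions section offers only a merged mild-to-moderate. A reader cannot tell whether objective 1 is about Hb <8 or Hb <11.
2. **The lowest values are in no stated anemia comparison.** An Hb of 4.5 is critical and not severe, and critical appears in neither the objective nor the analysis sentence. On the literal wording, a child kept at 5.5 instead of 4.5 adds a severe measurement.
3. **The 8 to <11 band does not have to fall when a drug works.** Children leave it at the top and enter it from below, so its direction depends on which flow is larger.

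At stake is the answer to secondary objective 1, and its comparability with the Hb <8 result that the protocol cites as motivation.

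**Working it through.** The protocol gives no sample size, power or event figure for anemia, so there is no stated figure to reproduce. The first two consequences follow from setting the sections side by side:

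| Place in the protocol | Categories used |
| --- | --- |
| Secondary objective 1 | moderate; severe |
| Statistical analysis paragraph | mild; moderate; severe |
| Definitions | mild-to-moderate (8 to <11); severe (5 to <8); critical (<5) |
| Background, local cohort | moderate or severe = Hb <8 |
| Executive Summary and background, Tanzanian trial | severe = Hb <8 |

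Only severe is common to the first three rows, and its defined band stops at 5.

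The third consequence needs arithmetic.

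**Inputs.** From the background: P(Hb <8) of nearly one-third, taken as 33%; P(Hb <11) above three-quarters, taken as 75%, 80% and 90% to show a range. Assumed: Hb is normally distributed and the drug shifts the whole distribution upward.

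**Formulas.** SD = 3 / (z(P<11) − z(P<8)); mean = 8 − z(P<8) × SD; band = P(<11) − P(<8).

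**Fit for 33%/75%.** z(0.33) = −0.4399 and z(0.75) = 0.6745, so SD = 3/1.1144 = 2.69 and mean = 8 + 0.4399 × 2.692 = 9.18 g/dL. The same steps give mean 9.03, SD 2.34 for 33%/80%, and mean 8.77, SD 1.74 for 33%/90%.

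**Results** (percent of infants, from unrounded values):

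| Fit | Shift (g/dL) | 8 to <11 | 5 to <8 | <5 | <8 | <11 |
| --- | --- | --- | --- | --- | --- | --- |
| 33/75 | 0 | 42.0 | 27.0 | 6.0 | 33.0 | 75.0 |
| 33/75 | +0.5 | 42.2 | 22.5 | 4.1 | 26.6 | 68.7 |
| 33/75 | +1.0 | 41.0 | 18.2 | 2.7 | 20.9 | 61.9 |
| 33/80 | 0 | 47.0 | 28.7 | 4.3 | 33.0 | 80.0 |
| 33/80 | +0.5 | 47.8 | 23.0 | 2.6 | 25.7 | 73.5 |
| 33/90 | 0 | 57.0 | 31.5 | 1.5 | 33.0 | 90.0 |
| 33/90 | +0.5 | 60.6 | 22.6 | 0.7 | 23.4 | 84.0 |

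At +0.5 g/dL the mild-to-moderate band is flat or higher in every fit, while Hb <8 falls to between 23.4% and 26.6%. At +1.5 g/dL the band is below its starting value in all three fits (38.7%, 44.0%, 56.6%). The cumulative columns <5, <8 and <11 fall with every upward shift.

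In these fits 1.5% to 6.0% of infants lie below 5. In the 33/75 fit that is 6.0/33.0 = 18% of those below 8, all outside the defined severe band.

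**The case against.** **The reversal is small or absent for large effects.** A reader might infer that an effective drug would show a sizeable increase in mild-to-moderate anemia. The documents do not support that. If the normal fits are shifted until Hb <8 is about halved, to 17%, the ratio of the 8 to <11 band after to before is 0.94 with P(<11) at 75%, 0.95 at 77% (44% to 42%, with Hb <11 at 59%) and 1.07 at 90%. A large rise needs nearly every child lifted above 8 to stop below 11; in the extreme case the band goes from 75 − 33 = 42.0% to 75 − 16.5 = 58.5%. A rise beside a fall in severe anemia would also not normally be read as harm. What stands is that the band is not a monotone measure of benefit.

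**Children below 5 may still be counted.** A reader might infer that the most severely affected infants drop out of the severe category altogether. The protocol does not say whether a child is classified by first, worst or any value, and that rule can properly sit in a statistical analysis plan. A child measured at 5 to <8 and later below 5 could still count as severe. The exclusion is certain only for the measurement below 5. Such children are not ignored elsewhere: hospital transport is described under Risk/benefit information, critical-anemia hospitalizations go to the DSMB within a week, and all-cause hospitalization is secondary objective 4.

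**Testing frequency.** Under Unscheduled visits, "All children who have a blood sample taken for malaria diagnosis or have signs or anemia will also have a hemoglobin measurement performed". A reader might infer a measurable bias, because the drugs should reduce such visits. The protocol gives no testing rates from which to size it. Making the scheduled 12-month Hb the main comparison is not a clear remedy either: it would replace prevention over the first year with a point prevalence in attending survivors, when the Sample Size section expects 10% loss and 13% mortality.

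**Background terms come from other studies.** That is true, but the gap between objective, definitions and analysis lies within this trial's own sections.

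**Conclusion.** The point holds as a mismatch between the stated definitions and the stated comparisons. Two parts need no distributional assumption: moderate has no cut-off and conflicts with the background's Hb <8 usage, and a measurement below 5 belongs to no category named in the objective or the analysis. The third, that the 8 to <11 band can stay flat or rise under a working drug, follows from the band's construction. Its size is illustrative and rests on normality, a uniform shift and the rounded local frequencies. In the same fits the severe band itself falls with benefit, so a misleading direction there is possible in principle but not shown.

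Severity is moderate. Anemia is a secondary endpoint with no power claim, and the primary analysis of clinical malaria is untouched.

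**What to change.** Define the efficacy categories cumulatively: any anemia, Hb <11; severe anemia, Hb <8, including values below 5; critical anemia, Hb <5. Reword secondary objective 1, its copy in the Executive Summary, the Definitions section and the analysis sentence so that all use these three categories. Either drop moderate or give it an explicit cut-off. The bands can be kept for descriptive tables.

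The cost is an amendment of wording in four places, best made before unblinding because the cut-off can affect the conclusion. Hb is recorded as a number on the Hemocue, so no new measurements are needed. The Hb values that trigger clinical care are not part of this change.
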